### Data collection

#### Spring and autumn questionnaires

The first main data collection commenced in autumn (2010 for Wave 1, 2011 for Wave 2). The participants’ basic anthropomorphic measures were collected, spirometry conducted and a health questionnaire completed. Height was measured using portable stadiometers (Seca 214), and weight with Tanita TIHD316 scales.

Pre- and post- bronchodilator spirometry was carried out, following ATS/ERS 2005 Task Force Guidelines [69], using a portable ultrasonic spirometer (Easy One™). Subjects performed the tests seated. All community workers were trained to perform spirometry to ATS/ERS standards. FVC, FEV_6_, FEV_1_, PEFR, and FEF_25-75_ were recorded. Participants were encouraged to perform three acceptable manoeuvres, within a maximum of eight attempts. Participants who refused to attempt spirometry were not excluded from the study. Post-bronchodilator spirometry was conducted 30 minutes after the administration of 400 micrograms salbutamol (Ventolin®) via a Volumatic® spacer.

The questionnaire for the primary participant included sections on respiratory health, health care usage, general health, co-morbidities and quality of life, as well as tenure, heating used in the dwelling and house quality.

Similar data, except for height and weight, were collected during subsequent spring and autumn data collections. One or more data-loggers (HOBO or iButton®) monitoring the temperature (and, for a subset of dwellings, humidity) in the dwelling were placed in winter and collected in spring.

If another adult was living in the dwelling they were also invited to fill in a shorter ‘support person’ questionnaire, including sections on respiratory health, general health and the effects on caregivers of caring for the person with COPD on their life.

#### Summer and winter diaries

Participants were asked to fill in over two-week periods during summer and winter, a detailed diary asking about activity, symptoms, medication, and medical care used.

#### Other data

Objective data on health care usage were found using participants’ National Health Index (NHI) to access hospitalisations. Primary care data were obtained from Primary Healthcare Organisations directly and via the Healthlink network. Objective assessments of electricity usage were obtained from electricity companies (Table 2).

**Table 2 T2:** Outcome measures

	
Primary outcome measure	Number of Moderate and severe exacerbations of COPD
Secondary outcome measures A	Severe exacerbations of COPD for which hospitalisation (ICD-10 code: J44) is required to treat the exacerbation;
	Moderate exacerbations of COPD; defined as requiring treatment with systemic corticosteroids and/or antibiotics.
	Hospitalisations for key lower respiratory tract illnesses (ICD-10 codes: J40-J47)
	All-cause hospitalisation
	Temperature in the living and bedrooms
	Electricity usage
	Costs to health care system
Secondary outcome measures-B	Self-reported quality of life
	Respiratory health of other people living in household
	Any changes in COPD severity (i.e. change in FEV1)
	Study withdrawals due to death or greater dependency
	Net benefits (benefits relative to costs) of the intervention.
	Support person burden

#### Outcome measures

**Acceptability of methods** The overall feedback from the majority of the participants in the WHEZ Study has, to date, been very positive. One such indicative report from a Wellington interviewer described her assessment of participants’ experiences in more detail:

“Although at the initial visit some participants had concerns and were unsure about the study, once they were given more information and further explanation of the study then they willingly and happily participated. In the first year pre-winter visits most of the participants reported how cold and damp their homes were and with the escalating cost of electricity they had to minimize how often they could have the heaters on to warm their homes. In the post–winter visit, the first wave of participants that received the subsidy of $500 commented how grateful and thankful they were for the subsidy because it helped tremendously - especially with the high winter electricity power bills. They also reported on the change in warmth in their homes since they had been insulated.”

### Data analysis

Generalised linear models will be fitted to the data. Covariates potentially included in the model will be study arm, current medication, age, sex, region, baseline severity, smoking status and immunisation status (influenza and pneumococcal). The appropriateness of a Poisson or negative binomial model of exacerbations will be confirmed by examining the residuals of the observed data fitted to the postulated models against an envelope of residuals from a set of simulated trials. If the observed residuals fall inside the simulated envelope then the model is considered to fit adequately. A non-parametric test – rank analysis of covariance – will be used to confirm differences between the groups.

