### Wave design and randomisation

As winter was the crucial period for the study, and recruitment is often slow at the start of the process the study was deliberately designed to recruit over two years in ‘waves’. Participants were recruited from three communities from 2009 to early 2011. Those recruited (i.e. consent and baseline data received) by June (early winter in the southern hemisphere) 2010 were assigned to Wave 1, those recruited later were assigned to Wave 2. Each wave was randomised into early and late intervention groups – the early group receiving the intervention the first winter in which the wave was enrolled in the study, and the late group the following winter. Thus *Wave 1- Early* participants received the fuel subsidy during 2010; *Wave 1- Late* and *Wave 2- Early* participants received the subsidy during 2011; *Wave 2- Late* participants received the subsidy during the winter of 2012. The randomisation was carried out by a statistician external to the study team.

The configuration of an autumn baseline with a spring follow-up was chosen in recognition of the significant illness of the sickest participants; with a full winter baseline there could have been more of a bias towards only the least unwell people completing the study. We allowed for a greater drop-out rate than we usually experience due to the illness among the study population.

As the intervention was carried out at a dwelling level, in order to avoid clustering, we selected only one primary participant per household, the person best able to complete the study questionnaire. The baseline interviews were carried out before randomisation so that knowledge of their group allocation could not affect the participants’ measures. In order to utilise the voucher for additional heating, the participants were then informed of their group allocation. Although the interviewers also knew the participant’s group allocation, they were trained to avoid mentioning group allocation status during interactions with the participants to minimise any recall bias. The analyses will be carried out with the researchers blinded to the meaning of the intervention group code. We also included several indicators designed to measure each participant’s propensity to report positive change and will control for the placebo effect by conducting sensitivity analyses using these propensity to positivity scores.

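### Current medication is listed as a covariate with no time point, although steroid or antibiotic treatment after allocation is part of the primary outcome; wave is missing from the list

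*Protocol article*

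**What the plan says.** The Data analysis section plans generalised linear models for exacerbations and gives one sentence on adjustment: "Covariates potentially included in the model will be study arm, current medication", followed by demographic variables (age, sex and region), severity at baseline, smoking, and influenza and pneumococcal immunisation. Severity carries the word baseline; medication, smoking and immunisation carry no time point. Wave is not in the list.

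Table 2 gives the primary outcome as "Number of Moderate and severe exacerbations of COPD". It describes the moderate ones as "defined as requiring treatment with systemic corticosteroids and/or antibiotics".

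On timing, Wave design and randomisation states that "The baseline interviews were carried out before randomisation" and that "the participants were then informed of their group allocation". The same section says that each wave was randomised into early and late groups. After that point, the questionnaire section reports "Similar data, except for height and weight, were collected during subsequent spring and autumn data collections", and the summer and winter diaries are "a detailed diary asking about activity, symptoms, medication, and medical care used".

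The Cost-benefit analysis section says the study will estimate and value changes in drug use, and so treats medication as something the voucher may alter.

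**The concern.** A covariate in the primary model should not be affected by the intervention, and still less be a component of the outcome. If current medication is read from a follow-up questionnaire or a winter diary, a participant taking antibiotics or systemic steroids for an exacerbation is counted in the outcome and flagged in the covariate. The covariate then absorbs part of the difference between arms, and the estimated rate ratio moves towards no effect. The trial was sized to detect a ratio of 0.75, so even a moderate shift matters.

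Wave raises a separate point. Randomisation was done within wave, and the two waves had different first winters (2010 and 2011), with the Christchurch earthquakes falling between and during them. A model that follows the randomisation would include wave, and the stated list does not.

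**Working it through.** **1. Is a post-allocation value available?** The questionnaire is completed before randomisation, allocation is then disclosed, and similar data are collected at later spring and autumn visits. The diaries ask about medication. Medication values therefore exist both before and after allocation, and the covariate sentence does not choose between them.

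**2. Does it overlap the outcome?** The outcome counts moderate and severe exacerbations. Moderate means treated with systemic corticosteroids and/or antibiotics. A post-allocation medication variable that includes such courses shares events with the outcome.

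**3. How far could the estimate move?** Inputs from Sample size: yearly rates 1.13 and 0.85, negative binomial k = 0.46. The plan's own ratio reproduces: 0.85 / 1.13 = 0.752, given as 0.75.

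Counts were simulated for 200,000 participants (gamma frailty with k = 0.46, one year, no loss to follow-up). A negative binomial model with k held at 0.46 was fitted on arm plus an indicator. The indicator equals 1 if at least one of the participant's exacerbations is captured by the medication variable. The captured share is an assumption, because the documents give none.

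| Adjustment | Estimated rate ratio |
|---|---|
| None | 0.753 |
| Post-allocation indicator, 10% captured | 0.776 |
| 25% captured | 0.803 |
| 50% captured | 0.844 |
| 80% captured | 0.869 |
| Pre-allocation indicator (same frailty, 50% captured) | 0.754 |

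**4. Hand check of the upper end.** If every exacerbation is captured, the indicator means at least one exacerbation, and the adjusted ratio is essentially the ratio of means among those with at least one.
- P(0) = (1 + k·m)^(−1/k).
- For m = 1.13, P(0) = 0.403 and the conditional mean is 1.13 / 0.597 = 1.891.
- For m = 0.85, P(0) = 0.488 and the conditional mean is 0.85 / 0.512 = 1.660.
- The ratio is 1.660 / 1.891 = 0.878, which agrees with the simulated trend.

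**5. Completeness of the listed covariates (Table 1 denominators, 522 enrolled).**
- Pneumococcal status is known for 420: 522 − 420 = 102, and 102 / 522 = 19.5%.
- The largest denominator in the table is 463 (daily smoking, among others): 522 − 463 = 59, or 11.3% of those enrolled.
- Beyond that best-answered item, pneumococcal status costs 463 − 420 = 43, and 43 / 463 = 9.3%.
- Without pneumococcal status the smallest denominator among the listed covariates that Table 1 reports is age, at 455. Dropping that item alone therefore still leaves a complete-case loss of at least 522 − 455 = 67 (12.8%).

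**The case against.** The strongest reply is that the article never says follow-up values will be used. Table 1, a baseline table, has an item on currently smoking daily, so the authors do use the word current for a baseline value. Influenza and pneumococcal status are also reported at baseline. Repeated questionnaires do not show that repeated values enter the model. Nor does the article say that current medication means acute courses rather than regular therapy. On the ordinary baseline reading there is no bias (0.754 against 0.753). All of this stands, so the defect is an open time point, not a declared error. It does not remove the point: the same sentence ties severity to baseline and leaves medication untied, and the cost-benefit section treats drug use as a possible effect of the voucher.

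Some stronger readings are not supported:

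- A reader might infer that adjusting for immunisation or smoking would also bias the result. Their timing is unstated too, but neither overlaps the outcome, vaccination was encouraged for everyone, and nothing in the article suggests that the voucher changes either.
- A reader might infer that the model will discard a fifth of participants. The covariates are only potential, no complete-case rule is stated, and missing-data rules may sit in the full protocol or analysis plan. At least 59 of the 102 exceed what even the best-answered item can explain.
- A reader might go on to quote a loss of power. The usual two-sided negative binomial formula gives 289 per arm on the plan's inputs, not the stated 239, so a power figure from it would mix two problems. Also, 522 with the planned 15% loss leaves 522 × 0.85 / 2 = 222 per arm, below 239 before any covariate is considered.
- A reader might infer that covariates will be picked to favour an arm. No selection rule is given, and the analysts are to be blinded to the meaning of the group code.

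**Conclusion.** The point holds in a limited form. The covariate list leaves the timing of medication open where a post-allocation value exists and would overlap the primary outcome. If such a value were used, a true rate ratio of 0.75 would be estimated at about 0.78 to 0.87 for captured shares of 10% to 80%. The direction is always towards no effect; the size depends on the assumed share, on annual rates and on k = 0.46. With pre-randomisation values the problem disappears.

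The omission of wave is a mismatch between the randomisation and the stated model. The article does not give the allocation ratio or event rates by wave, so no size can be attached to it.

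Missing covariate data are a secondary note: under complete-case analysis with pneumococcal status included, about 20% of the 522 could be lost, about 9% of 463 beyond the best-answered item.

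**What to change.** In the Data analysis section:

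1. State that every adjustment covariate is the value recorded before randomisation.
2. Define the medication covariate as maintenance therapy at baseline. Exclude acute steroid or antibiotic courses and any value recorded after allocation.
3. Replace the potential list with a set fixed before the analysis, and include wave in it.
4. State how missing baseline covariates are handled, for example by imputation or a missing indicator, so that no randomised participant is dropped. Removing pneumococcal status alone would not achieve this.

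The cost is a few sentences and minor programming. No new data are needed, because the baseline interview already precedes randomisation and wave is known for everyone.

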#### Cost-benefit analysis

The design of a cost-benefit analysis of this study is straightforward and follows similar studies’ methods [70,71]. The cost side of the intervention follows from providing a $500 voucher for electricity (and knowing the amount of electricity actually used). On the benefit side, the principal quantifiable outcome is reduced hospitalisations (ideally, exacerbation-reduced or exacerbation-free years would be measurable, but this was beyond the scope of the study). In addition, the study will estimate and value changes in pharmaceutical usage.

## Discussion

COPD is a growing problem in New Zealand and internationally, particularly as there are few proven effective interventions to reduce exacerbations. Although cold housing has been linked to respiratory illness, and respiratory infections linked to COPD exacerbations, only one previous study has directly examined the effect of indoor temperatures on COPD patients.

Being in a cold house during winter is likely to be a risk factor for COPD exacerbations. Many New Zealand households are living in fuel poverty with winter indoor temperatures regarded as unacceptable in other countries. In the WHEZ study we are addressing the houses’ thermal qualities and the effective cost of fuel. We have retrofitted insulation into the houses of vulnerable older people, which we have previously shown is an effective intervention to reduce fuel bills and increase the indoor temperature and in this study we are also subsidising the price of electricity, which indirectly has an impact on disposable household income.

While our intervention is modelled on the age-eligibility of the British Winter Fuel Allowance (households in which there is at least one person over 60), it is targeted and only includes older people who *also* have a chronic respiratory illness. In Britain a cash payment is made, whereas our intervention is paid directly into the participant’s electricity account and being in the southern hemisphere, these payments are *not* made just before Christmas and the holiday season. These factors make it more likely that the participants will spend the payment on additional heat.

New Zealand has no income support directly analogous to the Winter Fuel Allowance; however, it does have a heating supplement available to some people who receive a disability allowance, but this is only available to people on low income, who have regular on-going costs, above those of average people because of their disability or illness. Due to strict eligibility requirements, it is often difficult for low-income people to access this benefit and buy extra warmth as indicated by almost half the vulnerable participants in this study stating that they were colder than they would have liked because of the cost of heating; just over half had shivered inside the previous winter.

The WHEZ study is a staggered intervention community trial, which does not ‘blind’ the participants as to whether they are in the intervention or the control group. When participants were informed that they would be receiving the fuel subsidy, they were encouraged to see “heat as your medicine” and provided with sample calculations to help them estimate how much heating they could use without overspending the payment. The study is designed to explore the extent to which this supplement is effective for helping older people to maintain adequate indoor environments.

## Conclusions

We are successfully implementing a multi-centre, community-based, randomised control trial in partnership with community agencies and primary health organisations to see whether an electricity voucher enables elderly people with COPD to better heat their homes, and in turn, whether this reduces exacerbations of COPD symptoms, and hospitalisation.

The implementation has been complex and partly disrupted by a massive seismic event affecting the Christchurch region. However, the WHEZ study shows that it is possible to evaluate the merits of targeted welfare benefits for the health of people with chronic and debilitating diseases such as COPD, for whom an inability to keep warm is a common problem.

## Endnotes

^a^ When was the last time your COPD got so bad you needed to go to hospital? and b)When was the last time your COPD got so bad you needed to take antibiotics or steroids? The options for both questions were: Never/In the last year/1-3 years ago/ More than 3 years ago.

## Abbreviations

COPD: Chronic Obstructive Pulmonary Disease; WHEZ: Warm Homes for Elder New Zealanders (study)
